**CONFIDENTIAL**

**1.       Summary**

**- Type of Application**

A clinical trial of a medicinal product in new conditions.

**Two. - Title of clinical trial**

ABSORPTION AND SAFETY STUDY OF PALONOSETRON ADMINISTERED SUBCUTANEOUSLY IN CANCER PATIENTS.

**Three. - Protocol code**

EUDRACT: 2008-002853-19

Sponsor Code: PAL/SC-IV-2008

**June. - Clinical Research Ethics Committee.**

The study requires the approval of the Ethics Committee of Navarra.

**August. - Drug experimental and control: dose, dosage form, route of administration.**

- Experimental drug: ^®^ Aloxi (palonosetron)

Route of administration: subcutaneous (sc)

Pharmaceutical form of palonosetron hydrochloride ampoules

Dose: 250 μ g

Therapeutic group: A04AA

Laboratory Italfármaco

- Drug Control: Aloxi ^®^

Route of administration: intravenous (iv)

Pharmaceutical form of palonosetron hydrochloride ampoules

Dose: 250 μ g

Therapeutic group: A04AA

Laboratory Italfarmaco

Patients will be randomized to receive the first cycle via sc or iv. The second cycle will be managed by other means:

First stage: sc or iv administration, 30-60 minutes before chemotherapy administration.

Second stage: sc or iv infusion, 30 - 60 minutes before the administration of chemotherapy

**9. - Phase clinical trial.**

This is a Phase IV pharmacokinetic.

**10. - Main objective.**

Palonosetron explore pharmacokinetics when administered subcutaneously.

**11. - Design.**

Open, crossover, controlled trial in two phases. There shall be a minimum washout period of 14 days.

**12. - A disease or condition under study.**

Cancer patients undergoing chemotherapy requiring antiemetics.

**13. - Primary endpoint.**

Be assessed palonosetron pharmacokinetic parameters following:

Cmax = maximum concentration.

AUC _0-t_ =               area under the plasma concentration-time curve to the last extraction (time t).

tmax = time to reach Cmax.

**14. - Study population and number of volunteers.**

Cancer patients undergoing chemotherapy emetic. Will include a minimum of 25 evaluable patients (with pharmacokinetic evaluation SC and IV administration).

**15. - Duration of treatment.**

The regimen is administered for two consecutive chemotherapy cycles, so that the total duration of treatment and observation period is 6 to 10 weeks, depending on the timing of administration of chemotherapy.

**16. - Timetable and expected completion date**

Start Date:                                           September 2008

Recruitment end date:                             June 2009

Date of completion of treatment:               August 2009

***3.1.*** ***Abbreviations***

| AA | Adverse event |
| --- | --- |
| Competent Authority | Spanish Agency of Medicines and Health Products |
| AntiHBc | Virus core antibody B |
| AUC, AUC _0 -_ _∞,_ AUC 0-t | Area under the plasma concentration curve over time; extrapolated to infinity, to the last quantifiable extraction |
| BPC | Good clinical practice |
| BPL | Good Laboratory Practice |
| CEIC | Clinical Research Ethics Committee |
| Cmax | Maximum concentration |
| CRD | Notebook data collection |
| ECG | Electrocardiogram |
| VET | Specialty pharmaceutical advertising |
| EMEA | European Medicines Agency |
| FC | HR |
| FR | Respiratory |
| GGT | Gamma glutamyl transpeptidase |
| GOT (AST) | Aspartate amino transferase |
| GPT (ALT) | Alanine amino transferase |
| HBsAg | Australia Antigen B virus |
| HC | Medical record |
| BMI | í body mass index |
| mg, kg | Milligrams; kilograms |
| ml; L | Milliliters, liters |
| mm Hg | Millimeters of mercury |
| ND | Not determined |
| º C | Degrees Celsius |
| RD | Royal Decree |
| t _½_ | Elimination half-life |
| T ª | Temperature |
| TA, TAS, TAD | Blood pressure, systolic blood pressure, diastolic blood pressure |
| tmax | Time to reach Cmax |
| UIC | Clinical Research Unit |
| HIV | Human immunodeficiency virus |
| VSG | Erythrocyte sedimentation rate |

***3.3.*** ***Study Report***

The final report of the study is the responsibility of the Principal Investigator, the development of the analytical report shall be provided by the director of the analytical study.

**4** **JUSTIFICATION OF THE STUDY**

The study objective is to ascertain the pharmacokinetics of palonosetron after administration of the current formulation, Aloxi ^®,^ subcutaneously. In a previous study, the research team evaluated the possibility of administering granisetron subcutaneously, showing good results and adequate pharmacokinetic tolerance ([name] 2007). Palonosetron is a more potent drug with a longer elimination half-life, which justifies a greater and more lasting. Therefore to assess the possibility arises to administer the drug subcutaneously.

Palonosetron used in the prevention of vomiting associated with moderately or highly emetogenic chemotherapy. At present there is a preparation for intravenous administration, but sometimes facilitate subcutaneous administration handling these situations. This is the interest of the research team, know the feasibility of administering the drug by this route, from the formulation for intravenous administration.

***4.1.*** ***Pharmacological aspects***

Antagonists 5-HT _3_ receptors are a family of important antiemetics to prevent emesis induced by cytostatic high emetogenic as cisplatin and lack of antidopaminergic activity. Have identified a range of different chemical structures with anti-5-HT3 receptors (ondansetron, granisetron, tropisetron, dolasetron, palonosetron etc ...). The differences between them lie in the chemical structure and the pharmacokinetic behavior, and its levels of effectiveness and side effect profile quite similar.

Currently antagonists 5-HT _3_ receptors are used as first line treatment in virtually all patients who receive highly emetogenic chemotherapy regimens (platinum regimens containing anthracyclines or other cytostatic high dose) in patients expected the emergence of side effects with metoclopramide or in those with inadequate response to previous treatment.

Palonosetron is an antiemetic agent, serotonin antagonist with high affinity for the 5HT _3_ receptor. It is the most potent antagonist in the treatment group. Prevents the occurrence of vomiting with a power between 2 and 93 times higher than that observed with ondansetron or granisetron.

*4.1.1.*        *Clinical Use*

Palonosetron is indicated for the prevention of acute nausea and vomiting associated with cancer chemotherapy moderately and highly emetogenic.

*4.1.2.*        *Pharmacokinetics*

Pharmacokinetics of palonosetron have been evaluated when administered parenterally. Bioavailability is not known in other ways.

Plonosetron shows linear kinetics μ between 0.3 and 90 g / kg (Eisenberg 2004).

It is widely distributed in the body, presenting a volume of distribution of 6.9 to 7, 9 l / kg (Sloltz 2004). The plasma protein binding is not high, about 62%.

The 40% of the administered drug is excreted in urine, 50% is converted by hepatic metabolism, mainly by the liver microsomal system. Mainly involved in the metabolism isoenzymes CYP2D6 and to a lesser extent, CYP3A4 and CYP1A2. Despite this involvement of cytochrome, has not been observed that the genetic polymorphism affecting the elimination of palonosetron.

The half-life of palonosetron is about 40 hours with a total clearance of 173 ml / min and the renal 53 ml / minute.

No change was observed in the pharmacokinetics in the elderly, renal or liver failure.

Palonosetron did not inhibit or induce cytochrome CYPP450. Nor has any suffered no interaction with drugs, inhibitors or inducers, administered concomitantly.

| **Pharmacokinetic parameters** | **Mean (CV)**  **n = 12** | **Mean (CV)**  **n = 11** | **Mean (**± **SD)**  **n = 11** |
| --- | --- | --- | --- |
|  | Hunt 2005 | Shah 2006 | Eisenberg 2004 |
| ***Dose mg*** | 0.25 | 0.25 | 3 μ g / kg |
| ***Infusion time (seconds)*** | 10 | 15 | 30 |
| ***AUC*** ***_0-24_*** **(ng** × **h / l)** | 8,900 (22%) | - | ± 8.570 4.220 |
| ***AUC*** ***_0 -_*** *_∞_* **(ng** × **h / l)** | - | 20,700 (25%) | ± 35,800 20,900 |
| ***Cmax*** **(ng / l)** | 1,130 (61%) | 919 (44%) | ± 5.630 5.480 |
| ***t*** ***_1/2_*** **(h)** | 42.8 (25%) | 37 (24%) | 56.4 ± 5.8 |

*4.1.3.*        *Adverse Reactions*

Palonosetron, a single dose administered before chemotherapy is well tolerated in general (Siddiqui 2004):

Side effects reported most often in connection with the administration of palonosetron were headache (9%) and constipation (5%).

*4.1.4.*        *Precautions*

Use cautiously in patients with constipation or signs of intestinal obstruction, because I could make symptoms worse.

Although no ECG changes observed with palonosetron, caution should extermarse when used concomitantly with drugs that prolong the QT interval of the ECG, as is done with other 5-HT _3_ antagonists.

**5.** **STUDY OBJECTIVES**

***5.1.*** ***Primary Objective***

To explore Palonosetron absorption after subcutaneous administration, as compared with intravenous administration.

***5.2.*** ***Secondary objective***

To assess the local tolerance of palonosetron (VAS pain, skin changes).

**6.** **TYPE OF TEST REPORT AND STUDY DESIGN**

***6.1.*** ***Type of clinical trial***

Pilot clinical trial Phase I, single-center, open-label, single dose, with two periods of administration, controlled crossover study. It will randomize the sequence of administration of study medication.

***6.2.*** ***Randomization***

Subjects will be randomly assigned to each of the two treatment sequences.

The randomization number will be the one used to identify patients included in the study and will be reflected in the documents of the study.

Randomization was performed when deciding the administration of the first dose of medication. It will randomize the order of the route of administration under consideration by the list in Annex IX.

***6.3.*** ***Study Periods***

Selection phase: includes the 20 days before the start of the intervention phase. During this time, recruit volunteers, proving the suitability of the patient to participate in the study.

Study phase: consist sof two different treatment periods, separated by at least two weeks:

Both periods will be identical except for the route of administration the patient will receive, will depend on the randomization. Match management administration scheduled chemotherapy cycle.

Final review phase: includes the time from the completion of the intervention phase until the completion of the final visit, to be held in the next cycle.

***6.4.*** ***Design Justification***

The pharmacokinetic characteristics determine the estimated times of sampling, trying to define the likely tmax with subcutaneous administration and cover the entire absorption range.

The washout period is also conditioned by the terminal elimination half-life of palonosetron.

Since it is intended to assess bioequivalence, if not check if absorption occurs and what is the maximum concentration value is not considered appropriate to prolong the patient admission or request the removal of blood samples beyond the set range, which matches the patient's income for conrrespondiente chemotherapy.

Since there are no data on the absorption of subcutaneously palonosetron, pharmacokinetic analysis will be performed for the first four patients complete before continuing to include more patients. Special attention also to the local tolerance, but since it is a drug that is usually administered intravenously, with no evidence of phlebitis particular risk, it is considered that it should not have problems in this sense. Administration has been decided in the abdomen because it is necessary to administer a volume of 5 ml, since each vial contains the total dose diluted in this volume.

Using a dose of 250 μ g, which is the recommended sheet, in a single administration 30 minutes before administration of chemotherapy. Therefore maintaining marketing holder recommendation. In subcutaneous administration are to apply the same criteria.

**7.** **Population**

***7.1.*** ***Anticipated number of subjects***

The study will be conducted in 25 patients of both sexes. Since it is a crossover study in which each patient receives intravenous and subcutaneous administration, it is considered that 25 is a number sufficient to describe the pharmacokinetics of subcutaneously palonosetron, including bioavailability by this route.

***7.2.*** ***Inclusion criteria***

Patients must meet all of the inclusion criteria for participation in the study:

1. Patients requiring emetic chemotherapy of both sexes,
2. Age greater than 18 years,
3. ECOG ≤ 2.
4. Creatinine values ​​and normal liver function tests, considering an interval of 2 times the normal limits.
5. Adequate hematologic function defined by:
6. Absolute neutrophil count> 1,500 / mm ^3^ and WBC count> 3.000/mm ^3.^
7. Platelet count> 100,000 / mm ^3.^
8. Diagnosis of malignancy that needs treatment with chemotherapy with a moderate or high emetogenic potential (levels 3, 4 and 5 of Hesketh)
9. Have given written informed consent to participate in the study after having received all the information on it relating to design, objectives and possible risks resulting therefrom.
10. Ability to follow instructions and work together for the development of the study.

***7.3.*** ***Exclusion criteria***

None of the volunteers must submit any exclusion criteria, as it is referred to in the protocol:

1. Presence of infectious acute or chronic psychiatric disorders, clinically significant renal failure, at the discretion of the investigator.
2. Known hypersensitivity or intolerance to palonosetron.
3. Pregnant or lactating women with a positive pregnancy test.
4. Skin disorders that may interfere with the absorption of palonosetron, in the opinion of the investigator (edemas, inflammatory processes, thrombophlebitis ...).
5. Participation in another clinical trial with investigational products.

***7.4.*** ***Inclusion in the study***

After having given their consent in writing, once verified compliance with the inclusion and exclusion criteria, the patient was deemed eligible to participate in the study.

***7.5.*** ***Identification of participants***

Informed consent must be obtained in writing from each volunteer before any exploration.

The randomization number will be given after verifying that they have met all the inclusion criteria and none of the exclusion. This number will be determined by the scrambling, to be allocated before the administration of the first dose of study. This number will identify volunteers included in the study, and appear in all the documents of the trial.

The subjects will be identified also with 4 points, corresponding to the name (the first two) and two surnames.

Reference is made ​​to the full name and initials in identifying a list of subjects, which remain in the custody of the Principal Investigator. This list shall contain the identification of all patients signed informed consent, regardless of whether they were randomized after or not.

***7.6.*** ***Withdrawals and replacements***

Volunteers will be excluded from the study at their own request or by decision of the investigator when either of the following reasons:

intercurrent disease or AA if intolerable.

Violation of the foregoing restrictions.

Volunteer personal reasons for not continuing in the study.

Excluded subjects who leave the study for any of the above reasons will be replaced, to have a number of 25 evaluable patients, with complete pharmacokinetics of both routes of administration.

**8.** **Study Treatments**

***8.1.*** ***Drugs***

- Experimental drug: ^®^ Aloxi (palonosetron)

Route of administration: subcutaneous (sc)

Pharmaceutical form of palonosetron hydrochloride ampoules

Dose: 250 μ g

Therapeutic group: A04AA

Laboratory Italfarmaco

- Drug Control: Aloxi ^®^

Route of administration: intravenous (iv)

Pharmaceutical form of palonosetron hydrochloride ampoules

Dose: 250 μ g

Therapeutic group: A04AA

Laboratory Italfarmaco

Patients will be randomized to receive the first cycle via sc or iv. The second cycle will be managed by other means:

Both medications will be supplied by the promoter. It is the responsibility of the investigator administer the study medication according to the randomization code.

The medication is stored correctly labeled, according to the conditions proposed by the developer.

***8.2.*** ***Dosing Schedule***

This is a single dose study. Patients will receive on two separate occasions a single palonosetron dose of 250 μ g, once the administration is subcutaneous, intravenous in the other. The order of the route of administration will be allocated according to a randomization table.

*8.2.1.*        *Procedures medication administration*

The administration of medication will be as follows:

- First cycle: sc or iv administration, 30-60 minutes before chemotherapy administration.

- Second cycle: sc or iv infusion (the opposite way than first cycle), 30 - 60 minutes before the administration of chemotherapy

The order of the route of administration depends on the randomization table. The administration will be in the abdomen when subcutaneously. In the case of intravenous administration, the same route may be used in place for administration of chemotherapy or other medications that the patient should receive as their medical criteria.

Intravenous administration will be performed quickly, in 30 seconds, as described in the Product data sheet.

Subcutaneous administration will also perform at this time, in the abdomen.

*8.2.2.*        *Washout*

Has established a washout period between the two administrations of 14 days, which is considered sufficient as the pharmacokinetic data observed palonosetron in the literature.

*8.2.3.*        *Precautions, antidotes*

Available emergency equipment and standard operating procedure for the treatment of non-specific reactions (allergy, anaphylactic shock). At all times there will be a doctor reachable to respond to unforeseen developments.

*8.2.4.*        *Procedures blind*

It is an open, not hidden treatments either the researchers nor the volunteers, but for those responsible for drug quantification analysis.

*8.2.5.*        *Concomitant medication*

The investigator assessed the impact on the study in the event that any of the volunteers had to receive some treatment concomitantly.

Will try the two periods of administration of study medication are similar in concomitant medication.

*8.2.6.*        *Adherence*

Adherence will be secured by the research team, who directly administer the medication. Log the exact times of drug administration and removal of samples.

***8.3.*** ***Administration of study medication***

*8.3.1.*        *Labeling and distribution*

The products under investigation will be provided by the developer in sufficient quantities, they will get it directly from the manufacturer. The medication does not require any prior manipulation, is directly administered undiluted.

Upon receipt of trial medication, the Pharmacy shall duly completed (signed and dated) to the promoter acknowledgment of medication.

*8.3.2.*        *Storage and counting*

The records and inventory of the samples must be stored by the Pharmacy Service Center or by the investigator and will follow the following rules:

The investigator should retain the test samples at the pharmacy or store them in a safe and accessible only to persons authorized to dispense investigational drugs.

The inventory will be conducted by the researcher or pharmacist or other person designated by the former.

The inventory record shall detail the material received, and clearly indicated when and what subject was dispensed.

The register shall indicate the quantity and description of the research material that has at any time during the clinical trial.

At the end of this trial the researcher agrees to make the final inventory of the material and enter the result thereof in one form ″ ″ Medication count. The investigator or the pharmacist must return all materials to the promoter and other continent whether they are empty as if they still contain test samples.

The researcher agrees not to provide study drugs to anyone except those named as collaborating investigators and study volunteers.

**9.** **ASSAY DEVELOPMENT**

***9.1.*** ***Study Plan***

*9.1.1.*        *Selection stage*

In the 20 days before the start of the intervention phase of the study will be the selection of volunteers. This phase will recruit 25 patients will be informed of the design, objectives and possible risks of the study. Each patient will have the opportunity to ask any questions you want to research. Before any test is obtained written informed consent.

They perform a complete medical history that includes:

• Detailed anamnesis.

• Complete physical examination with assessment of functional status (ECOG scale).

• Registration of drugs administered to the patient at the time of inclusion.

• Laboratory tests:

Hematology: CBC.

Biochemistry: blood: cre atinina, urea, SGOT (AST), SGPT (ALT), GGT, total bilirubin, electrolytes

In case the patient has already been subjected to this analysis in the 10 days prior to administration of the medication can not be repeated.

With all these data verify the eligibility of patients to participate in the study.

*9.1.2.*        *Intervention phase*

The intervention phase will consist of two periods in which the patient will receive the study medication. Each will have a minimum duration of 12 hours, separated by at least two weeks washout period. In each volunteer will receive a dose of palonosetron 250 μ g intravenously or subcutaneously, according to the randomization code. Before the second administration of the drug is verify that the patient has adequate hepatic and renal function.

Will place a peripheral venous independent pathway by the patient receive chemotherapy and palonosetron, through which the blood samples drawn for determination of the drug.

They undertake every single day of intervention:

- Determination of the SBP and DBP, FC and temperature in a sitting position before administration of the study medication.

Blood drawn at baseline (5 ml).

Assessment of pain by visual analog scale.

After drug administration was performed:

Blood samples (5 ml) at the following times: end of infusion, 10 - 15 - 30 - 45 - 60 mins, 1,5 - 2 - 3 - 4 -8 to 12 hours. If income permits 24 hours.

Collection of urine during the 12 hours of study.

Subjective assessment of pain using a visual analog scale at the time: 1 to 4 and 8 hours.

Physical examination of the administration at 1, 4 and 8 hours after administration.

Each extraction with 5 ml of blood obtained. Samples were extracted in 5ml tubes through an Abbocath ® or a similar device placed in the arm contralateral to the administration of chemotherapy.

The track maintenance extraction will take place in optimum conditions by introducing, after each drawing 5 ml of a solution prepared with 1 ml of 1% sodium heparin, and 9 ml of 0.9% NaCl through the device.

Drawing the samples will be transferred into a glass with ice to the Laboratory of Clinical Pharmacokinetics Clinical Research Unit, where they are processed and frozen until analysis. The manipulation of the samples, the biological matrix and the storage temperature will be confirmed by the technician in charge of the analysis.

The determination of plasma concentrations of palonosetron be performed by HPLC.

*9.1.3.*        *Stage final review*

At least two weeks after the last drug administration, before the next cycle, check the patient's situation, using the same criteria as the selection period.

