**10.** **RESPONSE EVALUATION**

***10.1.*** ***Pharmacokinetic evaluation***

The quantification will be palonosetron concentrations in the Laboratory of Pharmacokinetics. Clinical Research Unit. University Clinic of Navarra. The Center is certified in Good Laboratory Practices.

With plasma concentration data at different times are calculated palonosetron pharmacokinetic parameters.

Primary parameters are considered in this study:

Cmax = maximum concentration. Its value will be extracted from the experimental data.

AUC _0-t_ = Area under the plasma concentration curve from time 0 to the last quantifiable concentration (time t) calculated by the trapezoidal method.

tmax =               time to reach Cmax. Its value will be extracted from the experimental data.

Security variables are:

VAS at different measurement times (baseline, and after the administration at 1, 4 and 8 hours)

Exploration of the administration at the same times.

The safety variables also include the description of the adverse events reported by patients or alterations in tests.

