An unexpected AA experience is defined as described not in terms of nature, severity or frequency in the investigator's brochure ..

*11.1.2.*     *Defining an adverse event causality*

The investigator will determine the relationship of any AA with study medication according to the following criteria (according to "Modified to the classification of Karch / Lasagna, Journal of the American Medical Association 234:1236-1241, 1975"):

*Short* : the reaction is with a reasonable time sequence after drug administration. The effect had previously been referred to or is an expected response to the study drug, confirming an improvement after the reduction or suspension of the drug and recurrence of effect after readministration of the same, with no apparent alternative etiology.

*Probable* : Reaction appears reasonable time sequence after drug administration. The effect has already been referred to previously or is an expected response to the study drug. Improvement occurs after reduction or discontinuation of treatment, and any other etiology is unlikely or less likely.

*Possible* : The reaction appears reasonable time sequence after drug administration. The effect had previously been referred to or is an expected response to the study drug. There is a possible alternative that may be responsible etiological AA.

*Unlikely* : the reaction does not appear with a time sequence after drug administration, or if exists, it is remote. The effect is not an expected response, or known to the study drug. There is a possible alternative that may be responsible etiological AA.

*Unrelated* : the AA is due to an underlying disease or concurrent or the effect of another drug and is not related to study medication (not to be related temporary or most likely alternatives exist).

The parameters of clinical and laboratory tolerance will be evaluated descriptively and differences using a Student t test (paired data), indicating hematological and biochemical parameters (See Annex IV for reference values) and BP, HR, RR and T ª, will be discussed and AA abnormal values. If any abnormality is observed, will convene again to volunteer to repeat this determination and this will be followed up until all changes are considered as clinically relevant.

*11.1.3.*     *Procedures for recording adverse events*

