**12.** **STATISTICS**

***12.1.*** ***Statistical methods***

The pharmacokinetic and statistical analysis of the data will be performed by UIC in the University Clinic of Navarra.

Pharmacokinetic analysis was performed on the data of concentrations of all evaluable volunteers completed the study as set forth in the protocol: pharmacokinetic profile with both formulations. The following pharmacokinetic parameters of palonosetron, will be determined for each subject following administration of each treatment:

-Cmax = maximum concentration,

-AUC _0-t_ = area under the curve versus time to the last quantifiable sample (time t), calculated using the trapezoidal method.

-Tmax = time of Cmax is reached,

-The elimination half-life, t _1/2_ , will be determined by the following expression:

t _½_ = ln 2 / k _e_

There will be a descriptive analysis of palonosetron pharmacokinetic parameters after subcutaneous administration.

Bioavailability is calculated in this way by calculating the ratio of AUC _0-t_ obtained after subcutaneous and intravenous administration.

Other parameters (analytical data, blood pressure) were analyzed using Student t test for paired data or ANOVA as appropriate, after having determined that the conditions for applying these tests. In the case of non compliance will be analyzed using appropriate nonparametric tests (Wilcoxon, Friedman).

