***12.2.*** ***Level of significance***

The level of statistical significance was set at *p* <0.05.

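### The planned paired t tests on vital signs and laboratory values do not match the measurement schedule: vital signs are taken only before dosing, respiratory rate is never scheduled, and every laboratory pair spans chemotherapy

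*Protocol*

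**What the plan says.** **Planned tests.** Section 11.1.2 says that clinical and laboratory tolerance will be described, with "differences using a Student t test (paired data), indicating hematological and biochemical parameters". The same sentence continues with "and BP, HR, RR and T ª, will be discussed and AA abnormal values". Section 12.1 adds: "Other parameters (analytical data, blood pressure) were analyzed using Student t test for paired data or ANOVA as appropriate", with Wilcoxon or Friedman as fallback. In section 12.2, "The level of statistical significance was set at" p < 0.05.

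**Vital signs.** On each dosing day section 9.1.2 lists "Determination of the SBP and DBP, FC and temperature in a sitting position before administration of the study medication". After dosing it lists blood samples, urine collection, a pain scale and "Physical examination of the administration at 1, 4 and 8 hours after administration". Section 10.1 confirms the last item as a timed safety variable: "Exploration of the administration at the same times". Sections 11 and 11.1 add an evaluation and a general adverse-event question at each blood sample, but no vital signs.

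**Respiratory rate.** It appears in the abbreviation list (section 3.1) and in the analysis sentence of section 11.1.2, but in no schedule.

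**Laboratory.** Tests fall at selection (section 9.1.1), before the second dose for hepatic and renal function only (section 9.1.2), and at final review at least two weeks after the last dose (sections 9.1.3 and 11.1). Section 8.2.1 places chemotherapy 30-60 minutes after each palonosetron dose.

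**The concern.** A paired t test answers the question set by its two time points. To show an acute effect of palonosetron on blood pressure, heart rate, respiratory rate or temperature, at least one member of the pair must be measured after the dose. None is scheduled. To attribute a laboratory change to palonosetron, the interval must not contain another treatment that moves the same values. Every interval here contains chemotherapy.

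The two groups of tests therefore fail in opposite directions. A non-significant vital-sign result carries no information about an acute effect. A significant laboratory result carries no information about its cause. A report that follows the plan could present both kinds of p value as tolerance evidence.

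**Working it through.** The protocol gives no power, effect size or standard deviation for these tests, so there is no stated figure to reproduce. The check traces each tested parameter to its scheduled times and then works out what the resulting pair can show.

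**Step 1: tests against schedule.**

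| Parameter | Test named in | Scheduled times | Pairs available |
|---|---|---|---|
| Blood pressure | 11.1.2, 12.1 | Before dose 1, before dose 2 | Pre-dose against pre-dose |
| Heart rate, temperature | 11.1.2 | Before dose 1, before dose 2 | Pre-dose against pre-dose |
| Respiratory rate | 11.1.2 | None | None |
| Hepatic and renal tests | 11.1.2, 12.1 | Selection, before dose 2, final review | Three, each spanning one or two cycles |
| Haematology | 11.1.2, 12.1 | Selection, final review | One, spanning both cycles and both routes |

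**Step 2: how much of dose 1 remains at the second pre-dose reading.** Inputs: minimum washout 14 days = 14 × 24 = 336 h; half-life 40 h (section 9.3), and 56.4 h as the longest value in the table of section 4.1.2. Fraction remaining = 0.5^(336 / half-life).

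- 40 h: 336 / 40 = 8.4 half-lives; 0.5^8.4 = 0.30%.
- 56.4 h: 336 / 56.4 = 5.96 half-lives; 0.5^5.96 = 1.6%.

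**Step 3: what the pre-dose pair can detect.** Simulation with 25 patients, two-sided alpha 0.05 and 20,000 runs. The effect acts after dosing, and about 1.6% of it carries over to the second pre-dose reading. Effects are in units of the within-patient SD of a single reading.

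| True acute effect (SD) | Rejection rate |
|---|---|
| 0 | 4.9% |
| 0.5 | 5.0% |
| 1 | 5.3% |
| 2 | 5.0% |

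The rate stays at the type I error level whatever the effect. The simulation puts no chemotherapy effect into the pair. In practice the second reading also follows the first chemotherapy cycle, so any real shift between the two would not point to palonosetron either.

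**Step 4: what the laboratory pair detects when palonosetron does nothing.** Let c be the mean chemotherapy shift divided by the SD of the within-patient difference. The protocol gives no value for c, so a range is assumed. With n = 25 the noncentrality is c × √25 = 5c on 24 degrees of freedom.

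| c (assumed) | Noncentrality | Probability of p < 0.05 |
|---|---|---|
| 0 | 0 | 5% |
| 0.3 | 1.5 | 30% |
| 0.5 | 2.5 | 67% |
| 0.8 | 4.0 | 97% |
| 1.0 | 5.0 | 99.8% |

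The laboratory test mainly reports whether chemotherapy moved the value.

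**The case against.** **The safety objective does not rest on these tests.** This stands. The secondary objective (section 5.2) is local tolerance. Section 10.1 builds the safety variables on the pain scale and site examination, both taken at 1, 4 and 8 h on both routes, plus adverse events and altered tests. Section 12.1 treats laboratory data and blood pressure as further parameters. A reader might infer that the trial cannot assess safety at all; the protocol does not support that.

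**The sentence in section 11.1.2 is garbled by translation.** It can be read as applying the t test to laboratory values only and merely discussing the vital signs. That weakens the point for heart rate and temperature. It does not remove it: section 12.1 independently tests blood pressure, and respiratory rate is still due to be reported without being measured.

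**A route contrast exists for some laboratory values.** A reader might infer that no contrast could separate the routes. That is too strong. Hepatic and renal values before dose 2 follow one route and those at final review follow the other; chemotherapy is common to both and sequence is randomised (section 6.2). However, that contrast is not planned, comes late after dosing, and excludes haematology.

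**Causality grading protects against misattribution.** Partly. The scale in section 11.1.2 lets an individual event be assigned to another drug. It does not correct a p value on a group mean.

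**Further material may settle it.** The data collection notebook (Annex I) is not shown and may list more measurements, and the physical examinations at selection and completion may include vital signs. Those examinations would fall before the study or after both chemotherapy cycles. A statistical analysis plan could choose the pairs, but it cannot supply post-dose readings that were never scheduled.

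**Multiplicity.** A reader might add a false-positive rate over all the tests. That would need a parameter count and independence that the protocol does not give, and would treat blood counts as unaffected by chemotherapy. It forms no part of this point.

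**Conclusion.** The mismatch between tests and schedule is real. The protocol schedules no post-dose vital-sign value on either dosing day and no respiratory rate at any time, so the vital-sign tests reject at about 5% regardless of any acute effect. Every laboratory pair contains at least one chemotherapy cycle. With no palonosetron effect, significance is expected in 30% to 99.8% of trials for assumed shifts of 0.3 to 1.0 SD of the within-patient difference. A significant laboratory change therefore cannot be attributed to palonosetron.

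This rests on the protocol text without Annex I, on 25 evaluable patients, on two-sided testing (sidedness is not stated) and on an assumed range for the chemotherapy shift. The conclusion about vital signs depends only on the schedule, not on the assumed range. The point is confined to the parameters named for these tests. Local tolerance and the primary pharmacokinetic analysis are untouched.

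**What to change.** Reconcile sections 9.1.2, 11.1.2 and 12.1 in one of two ways.

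1. **Measure what is tested.** Record blood pressure, heart rate, respiratory rate and temperature before dosing and again at the existing 1, 4 and 8 h contacts. Compare post-minus-pre change between routes within patient. State that this is a route contrast only: chemotherapy starts 30-60 minutes after dosing, so the 1 h reading falls at or after its start and the later ones follow it. The contrast also assumes similar chemotherapy in both cycles. The cost is 3 extra sets per period, 3 × 2 = 6 per patient, or 6 × 25 = 150 in all, at visits to the bedside that already take place.
2. **Test only what is measured.** Delete the vital-sign tests, and remove respiratory rate from section 11.1.2. Only uninformative p values are lost.

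Under either option, replace the laboratory paired t tests with descriptive shift tables from selection to final review (and to the pre-dose-2 value for hepatic and renal tests). State that changes across cycles are not attributable to palonosetron. This needs wording only and no new samples.
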